### Ethical Considerations

The study protocol has been approved by the ethics committees of Jingjiang People’s Hospital and Taizhou People’s Hospital (TZRY-LL-AF/SQ-018-3.0 and KY 2022-167-01). A cover letter will be provided to guarantee human rights and ethical transparency, and inform the participants about the aims and benefits of this study. Participants will be informed that they can voluntarily participate and withdraw from the study without any impact on their treatment or nursing care. If they agree to participate, they will be required to sign an informed consent form with detailed information concerning the goals and procedures of the intervention. The data of this research will be kept confidential and anonymous. The trial was registered in November 2022 at ClinicalTrials.gov (NCT05606549).

## Results

The research activities for this study commenced in October 2022. Participant recruitment and data collection began in February 2023, with the expectation of completion within 12 months (by December 2024). As of October 30, 2023, a total of 97 gastric cancer patients and their spouses have been recruited, and all baseline data have been collected. Once sufficient participants are recruited, subsequent measures will be performed and data analysis will commence. The primary results of this study are anticipated to be announced in June 2024.

## Discussion

### Marital Self-Disclosure Intervention and Protocol Design

Improvement of the fear of cancer recurrence and dyadic coping ability in patients with gastric cancer is necessary. To date, few psychological interventions effectively manage the fear of cancer recurrence in patients with gastric cancer. This is the first and only intervention with the explicit aim of improving the fear of cancer recurrence in Chinese patients with gastric cancer. The intervention focuses on personal emotional expression, social cognition expression, benefit discovery, and outlook to the future, with a further focus on the fear of cancer recurrence. This study will provide evidence of the effectiveness of the marital self-disclosure protocol for improving the fear of cancer recurrence compared with routine nursing care.

There are several advantages of the marital self-disclosure intervention. First, the study involves a long-term intervention that spans from the participant’s diagnosis of gastric cancer until the end of chemotherapy. In a preview study, among patients with gastric cancer in the first, third, and sixth chemotherapy stages, greater family support was associated with a lower fear of cancer recurrence [7]. Therefore, early and lasting intervention is essential.

Second, the study considers the marital factors related to the fear of cancer recurrence and has developed relevant communication topics in each phase. The husband and wife will be trained in marital self-disclosure, and formal disclosure will be made after both husband and wife have mastered the method of disclosure. Moreover, before each phase, the couple will review the method of disclosure again so that the couple can fully grasp the method of disclosure and return it as a homework exercise, making the research results more credible. Finally, this study combines written and verbal representations to facilitate better participant expression of concerns regarding the fear of cancer recurrence.

Third, the study is based on not only a literature review but also Chinese cultural background, clinical practice, and stakeholder input to design a feasible intervention for Chinese patients with gastric cancer.

Fourth, the marital self-disclosure intervention will be designed for implementation by nurses, and it may appeal to nurses who seek flexibility and dynamism in their work. The intervention will train nurses to teach patients and their spouses to use the theory of respect, empathy, and positive attention in emotional communication and marital interaction. Stable, friendly, and trusting relationships will be built between nurses and patients.

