### Methodology and Design

A quasiexperimental study with a nonequivalent (pretest-posttest) control group design will be used to examine the effect of marital self-disclosure on the fear of cancer recurrence and dyadic coping ability among patients with gastric cancer and their spouses. The study will be conducted at 2 tertiary hospitals in Taizhou City, Jiangsu Province, China. Considering the time constraints, sample availability, and prevention of contamination, the research will be conducted in the oncology departments (digestive system) of 2 hospitals. The 2 hospitals will be assigned randomly. A total of 42 patients with gastric cancer undergoing chemotherapy and their spouses will be recruited from each hospital. Eligible patients with gastric cancer undergoing chemotherapy who agree to participate and sign the informed consent form will be included in this research. Participants from Jingjiang People’s Hospital will be assigned to the experimental group, while participants from Taizhou People’s Hospital will be assigned to the control group. Patients with gastric cancer share similar characteristics, such as demographics, treatment, and nursing care plans. The treatment methods refer to the “Guidelines for Diagnosis and Treatment of Gastric Cancer” [32]. The chemotherapy scheme is selected according to the patient’s actual situation, which is predicted for 4 to 6 cycles. The study includes 4 stages of face-to-face interventions. The researchers will take measurements at 3 time points: baseline and 2 and 4 months postintervention.

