### Participants

#### Inclusion Criteria

##### Patients

The inclusion criteria for patients are as follows: (1) the disease meets the diagnostic criteria of the “Guidelines for Diagnosis and Treatment of Gastric Cancer” [32], the preoperative gastroscopy and pathological diagnosis indicate advanced gastric cancer, and the postoperative pathological classification is type II, III, or IV; (2) age ≥18 years and ability to write and communicate effectively; (3) the main caregiver is their spouse; (4) clear consciousness and no understanding barriers; and (5) written informed consent to participate in this study.

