### Sample Size

The sample size will be calculated using the following formula for sample size based on the study by Charan and Biswas [33]: sample size = 2 (SD) 2 × (Zα/2 + Zβ)2 / D2. It is based on the FoP-Q-SF (primary outcome) from a previously published study [15]. It showed a 95% power to detect a mean difference of 2.88 points between the control and experimental intervention groups in 61 Chinese patients with breast cancer. Statistical significance will be calculated to achieve a statistical power of 0.9 at a 5% significance level for 70 participants in each group. A 2-tailed test will be used to test the hypothesis. The sample size of each dependent variable is 35. To address dropout, an additional 20% is added to the calculation. As a result, the sample size for the experimental and control groups is 42. Consecutive sampling will be used in this study.

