#### Experimental Intervention

The marital self-disclosure intervention is divided into 4 stages. Each stage will be divided into the chemotherapy and hospitalization phase and the interval and home phase. Both phases include verbal and written disclosures, and the intervention will be conducted in 16 weeks. The flowchart of the trial is shown in Figure 1.

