##### Phase 1: Development of the Marital Self-Disclosure Intervention

A previous systematic study [35] by our team found that the most common methods of couple communication are one-on-one and face-to-face communication. They should accept training in marital communication methods before marital self-disclosure, such as how to incorporate the materials from the course into their daily lives through the communication skills learned [36], the strategies for expressing their thoughts and feelings about cancer, and the strategies for accepting and affirming each other’s feelings and opinions [23]. Psychological evaluation indicators are stable, and no significant changes are observed in frequent evaluations [15]. Therefore, 3 to 5 weeks per session can obtain a trend change in the index and will not lead to patient evaluation fatigue, which involves better evaluation frequency. Patients with cancer become unwell due to chemotherapy, and short-term interventions (3-6 stages, 40-60 minutes each step) increase memory and application of what couples have learned and increase patient confidence and motivation to manage their disease [37]. In situations where disclosure to a partner becomes challenging or problematic, individuals may gain some benefit from writing a disclosure diary [15,38,39]. The researchers have developed and designed the intervention. The literature mentions the disclosure needs of cancer couples and the changes in cancer patients’ fear of recurrence during chemotherapy, and provides information on the interview framework, objectives, benefits, mechanisms, and strategies to implement marital self-disclosure. To further improve the marital self-disclosure intervention, the researchers will conduct in-depth interviews with 3 patients with gastric cancer and their spouses to explore the experiences and needs of marital communication. Furthermore, 6 nurses from the oncology ward will be interviewed to explore the intervention preference and obtain their suggestions for the content of marital self-disclosure. The findings of in-depth interviews will be used to improve the frame, stage, time, and disclosure process of marital self-disclosure.

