### Limitations

This study has some minor limitations. First, this study involves a long-term intervention, and some participants may not complete the study owing to loss of follow-up or physical deterioration during treatment. Second, missing data may influence the results and must be addressed statistically. To overcome this bias, a 20% attrition rate will be included in the sample size calculation, and an intention-to-treat analysis will be performed during the data analysis. Finally, this study will only include patients during chemotherapy.

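### Chemotherapy cycle at entry is not fixed, listed or modelled, so a difference in treatment phase between the two hospitals could not be told apart from the intervention

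*Protocol article*

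**What the plan says.** The Discussion (Marital Self-Disclosure Intervention and Protocol Design) gives as the first advantage that "the study involves a long-term intervention that spans from the participant’s diagnosis of gastric cancer until the end of chemotherapy". The Methods describe something narrower.

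- **Entry.** Methodology and Design: "Eligible patients with gastric cancer undergoing chemotherapy who agree to participate and sign the informed consent form will be included in this research". The patient inclusion criteria also require that "the postoperative pathological classification is type II, III, or IV", and Limitations states that "this study will only include patients during chemotherapy". None of the numbered inclusion or exclusion criteria names a cycle at entry or a minimum number of cycles still to come. Sample Size adds: "Consecutive sampling will be used in this study".
- **Dose.** Methodology and Design describes a chemotherapy scheme "which is predicted for 4 to 6 cycles". The Chemotherapy and Hospitalization section gives one session per chemotherapy, four in all. Experimental Intervention says that "the intervention will be conducted in 16 weeks". Table 2 labels the four topics first to fourth chemotherapy.
- **Controls.** Outcome Assessment has the control group reassessed at the same intervals as the experimental group. No text ties its baseline to a cycle.
- **Data and model.** Sociodemographic and Clinical Variables lists pathological classification, tumor stage, treatment type and time since diagnosis, but not cycle number. Data Analysis specifies a two-way repeated-measures ANOVA (group and time) by intention to treat. Under Allocation and Blinding, each arm is one hospital.

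**The concern.** Arm and hospital coincide, so nothing in the allocation balances the cycle at which couples enter. If one hospital tends to enroll at the first cycle and the other across the course, the two arms are at different points of treatment at baseline, month 2 and month 4. The group-by-time term then carries treatment phase together with the intervention.

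The article gives some reason to think that phase matters for the primary outcome. The Introduction says that adverse reactions to treatment heighten fear of recurrence, and Phase 1 of the intervention's development refers to literature on "the changes in cancer patients’ fear of recurrence during chemotherapy". Phase 1 also describes psychological indicators as stable under frequent evaluation, so neither size nor direction can be taken from the text.

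A second, conditional issue concerns the experimental arm alone. A couple that enters late in the course runs out of chemotherapy admissions before the fourth session, yet stays in the intention-to-treat analysis. Table 3 defines the last measurement as following the fourth intervention, which such a couple does not reach.

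**Working it through.** No figure in the plan is in question here, so none is reproduced. The check is a count of sessions and of time since chemotherapy.

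**Inputs.** Planned cycles N = 4, 5 or 6 (Methodology and Design). One session per chemotherapy, four in total (Chemotherapy and Hospitalization). Duration 16 weeks (Experimental Intervention). Spacing of 3 to 5 weeks per session (Phase 1). Cycle at entry k is not given.

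**Step 1: sessions possible.** Cycles left, counting the entry cycle, are r = N − k + 1. Facilitated sessions possible = min(4, r).

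| N | Sessions possible for entry at cycle 1, 2, 3, … | Latest entry for four (k = N − 3) |
|---|---|---|
| 4 | 4, 3, 2, 1 | cycle 1 |
| 5 | 4, 4, 3, 2, 1 | cycle 2 |
| 6 | 4, 4, 4, 3, 2, 1 | cycle 3 |

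With r = 3, 2 or 1, the share of sessions is at most 3/4 = 75%, 2/4 = 50% or 1/4 = 25%.

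The share of patients who can receive all four depends on the distribution of k, which is unknown. If all enter at cycle 1, it is 100%. If entry were spread evenly over cycles (an assumption, for range only), it would be 1/4 = 25%, 2/5 = 40% and 3/6 = 50% for N = 4, 5 and 6.

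**Step 2: treatment phase at month 4.** Put the entry cycle at week 0 and space cycles s weeks apart. The last chemotherapy falls at week s(r − 1), so weeks since it at week 16 are 16 − s(r − 1). The article gives no cycle length. I take s = 16/4 = 4, with 3 and 5 as the range, which assumes that session spacing equals cycle spacing.

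| Cycles left r | 1 | 2 | 3 | 4 | 5 | 6 |
|---|---|---|---|---|---|---|
| s = 3 | 16 | 13 | 10 | 7 | 4 | 1 |
| s = 4 | 16 | 12 | 8 | 4 | 0 | −4 |
| s = 5 | 16 | 11 | 6 | 1 | −4 | −9 |

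A negative value means that the patient is still on treatment. These values apply to both hospitals. At s = 4, the month-4 measure can fall anywhere from 16 weeks after the last chemotherapy to before the course has ended, depending on entry cycle and planned cycles.

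**Step 3: the Discussion sentence.** At the start, postoperative classification and the chemotherapy setting place entry after diagnosis and surgery. At the end, a couple starting at cycle 1 has N − 4 = 0, 1 or 2 cycles without a session. The sentence matches the Methods at the end only when four cycles are given, and at the start not at all.

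**The case against.** The strongest reply is that early entry is evidently intended. Table 2 numbers the sessions by chemotherapy from first to fourth, four sessions match the minimum of the predicted cycles, and the same Discussion paragraph argues for early intervention. Being on chemotherapy may simply describe the setting. With entry at cycle 1, every patient who has 4 to 6 cycles can receive all four sessions. This carries weight for the experimental arm: dilution is unlikely if the table means what it appears to mean. But session labels are not an entry criterion, they could mean the first chemotherapy after enrollment, and they cannot anchor a control hospital that has no sessions.

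It can also be said that the article condenses a fuller protocol, where an entry window or covariates may stand. That is fair, and I do not treat the absence of an operational window as an error in itself. The article does, however, print full criteria, a variable list and the primary model, and cycle appears in none of them.

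The nonequivalent design is openly declared. Baseline outcome, time since diagnosis, treatment type and tumor stage are collected, and baseline characteristics are compared. These are partial safeguards; time since diagnosis is only a rough proxy for cycle number.

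A reader might go further and infer that late-cycle patients are being enrolled and the effect diluted, or that the hospitals do differ in phase and the result is biased. The documents support neither: they describe no late-cycle entry and give no distribution of entry cycle for either hospital.

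**Conclusion.** The point holds in a limited form. Entry cycle is left open by the printed criteria, is anchored only indirectly and only in the experimental arm, is not a listed variable, and is absent from the stated model, in a design where arm equals hospital. An imbalance is possible, not shown. Without the distribution of entry cycle and the difference in FoP-Q-SF by phase, no bias or power figure can be given.

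Loss of sessions is conditional on late entry in the experimental arm, and on facilitated sessions being tied to chemotherapy admissions as described. The Discussion sentence is inaccurate at its start, and at its end for courses of 5 or 6 cycles. It is descriptive text on which no rule or analysis depends, so it does not undermine the design.

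**What to change.** 1. For all couples, including the 97 already recruited, take cycle number at baseline and planned number of cycles from the chart, and report both by hospital.
2. Add cycle at baseline as a covariate in the primary FoP-Q-SF model, with its interaction with time; a main effect alone would leave the group-by-time contrast unadjusted. If the hospitals barely overlap in entry cycle, say so, because the adjustment then rests on extrapolation.
3. Run a sensitivity analysis in both arms limited to couples with at least four cycles left at entry.
4. If any couples are still to be enrolled, apply one entry point at both hospitals: first cycle, with at least four planned. This may affect few or none, since 97 couples already exceed the planned 2 × 42 = 84.
5. As a minor correction, reword the Discussion sentence to say that the intervention covers four chemotherapy cycles (about 16 weeks).

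The cost is two chart fields per couple, one covariate, a sensitivity analysis on a smaller sample, and possibly slower recruitment if enrollment continues. Adjustment deals with treatment phase only; other differences between the hospitals remain.

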### Limitations

This study has some minor limitations. First, this study involves a long-term intervention, and some participants may not complete the study owing to loss of follow-up or physical deterioration during treatment. Second, missing data may influence the results and must be addressed statistically. To overcome this bias, a 20% attrition rate will be included in the sample size calculation, and an intention-to-treat analysis will be performed during the data analysis. Finally, this study will only include patients during chemotherapy.

### Conclusion

This is the first attempt to develop a brief and feasible intervention to manage the fear of cancer recurrence in Chinese patients with gastric cancer. If the marital self-disclosure intervention is effective, it will be implemented at the hospital. This brief and focused intervention will be integrated to enhance clinical practice. Even with null results, participants with gastric cancer and their spouses will obtain more comprehensive self-care nursing knowledge. Furthermore, investigators will obtain a large amount of data to analyze the fear problems of patients with gastric cancer.

## Abbreviations

DCI: Dyadic Coping Inventory
FoP-Q-SF: Fear of Progression Questionnaire-Short Form
